#### Community volunteers

3.5.3

Inclusion criteria include: any age (including younger people of school age); Live, work or are willing to regularly come to the target LGA; currently a volunteer engaging with community members receiving *Connect Local* program; and understand and speak English sufficiently to understand the program.

Organisations engaging volunteers will share the information on the evaluation, and all volunteers who have been involved in supporting individuals engaging in *Connect Local* will be invited to reach out to researchers and participate in the evaluation.

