### Program effectiveness

3.1

Compared to the comparator group, older people receiving the intervention will, when compared to baseline, report at 3-, 6- and 12-months follow-up:

(i) a reduction in loneliness, social isolation and/or depressive symptoms;(ii) improvement in wellbeing and quality of life;(iii) increased access to activities/services in the community.

Three months after participation in the program, community volunteer participants will have improved wellbeing and quality of life when compared to baseline.

It is hypothesised that all stakeholders: intervention, volunteer and service provider participants will also have a positive perception of and experience with the program.

*Research question for older participant cohort using PICO:*

Does participation in the *Connect Local* social connection program reduce loneliness, social isolation and/or depressive symptoms, improve wellbeing and quality of life and increase access to activities/services in community of older Australians when compared to a similar group who do not have access to a similar program?

*Research question components for stakeholders using SPIDER:*

Sample: volunteers and service provider participants;

Phenomenon of interest: perception and experience of program;

Design: prospective surveys and semi-structured interviews;

Evaluation: impact on community and health services, and perceptions of the program;

Research type: mixed methods.

Question: What are the perceptions and experiences of volunteers/service provider participants after being a part of the *Connect Local* program?

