#### Older community members: intervention group

3.5.1

The inclusion criteria include being aged 65 years or older; understand and speak English sufficiently to understand and be involved in the program; live in the target LGA; community dwelling (including those experiencing homelessness); have at least one chronic health condition; are at risk or experiencing loneliness, social isolation and/or depressive symptoms. Screening tools are summarised in Table 2, loneliness will be assessed using both the Single Item Measure and UCLA-3 as per recommended national indicators of loneliness (66).

**Table 2 tab2:** Intervention outcome evaluation methods.

Evaluation component *Definition*	Indicators	Methods and tools
Individual level *Impacting individuals directly*	*Older person participants:*	
	Loneliness	Single-item measure of loneliness: How often do you feel lonely?, responses: often or always, some of the time, occasionally, hardly ever or never (often or always, some of the time indicating loneliness)	UCLA-4 (57)
UCLA-3 (score of ≥6 indicates at risk of loneliness) (58)
Social isolation	Lubben-6 (score ≤ 12 indicates at risk for social isolation) and − 18 (59);
Social anxiety	Mini-SPIN (Social Phobia Inventory, SPIN) (60);
Depressive symptoms	GDS-5 (score of ≥2 is indicative of depression) (61);
Wellbeing and quality of life	Physical wellbeing (and QoL): EQ-5D-5L (62); Mental wellbeing: Warwick-Edinburgh Mental Wellbeing Scale (WEMWBS) (63);
Goals attained^+^	Goal Attainment (64)^+^.
Perceptions of program^+^	Interviews on perceptions of the program^+^.
*Service providers:*	
Perceptions of program	Interviews/focus groups on perceptions of the program.
*Volunteers:*	
Wellbeing and quality of life	Physical wellbeing (and QoL): EQ-5D-5L (62); Mental wellbeing: Warwick-Edinburgh Mental Wellbeing Scale (WEMWBS) (63);
Perceptions of program	Interviews/focus groups onperceptions of the program.
Community level *Impacting broader community*	*Older person participants:*	
	Access to activities/services Number and types of services offered to participants	Resource use questionnaire [adapted from Fletcher et al. (65)]
	*Community service providers:*	
	Impact of program on community services	Community service impact survey [adapted from NHS (56)]
	Community service provider Satisfaction with program	Interview/focus group with community service providers

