#### Older community members: comparator

3.5.2

Given the proposed whole of community impact of *Connect Local* program, the inclusion criteria for the comparator group are the same as for the intervention group, except that they do not live in the target LGA. These participants will be recruited from the local tertiary hospital and aged and community care provider. All eligible individuals will be made aware of the program through their care provider and will be asked if their details can be shared with the researchers to contact them about the study. The researchers will contact the individuals to obtain consent. Recruitment will be monitored in blocks of five to match comparator participants by age and gender to the intervention participant group.

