##### Individual level

3.6.2.1

This is the level at which individuals are impacted directly, including older community members, volunteers and health and social service providers.

For older community members, we will consider the primary outcome as a mean change in loneliness, from baseline at 3, 6 and 12 months for participants receiving the *Connect Local* program, when compared to the comparator group. This will be measured using UCLA-3 as informed by previous research that support the sample size calculations (58). At this stage, there is insufficient research data to calculate sample size when using UCLA-4 (57), however this tool has been recommended for use by community organisations by Australia’s national network, Ending Loneliness Together (71), therefore we will also utilise this tool to capture loneliness to ascertain whether it can be utilised with this cohort in future studies.

As outlined in Tables 2, 3, secondary outcomes, including social isolation, social anxiety, depressive symptoms, and improvement in quality of life and wellbeing, are a mean change from baseline at 3, 6 and 12 months for participants receiving the *Connect Local* program, when compared to the comparator. Achieved goals, as measured by the Goal Attainment scale (64), will also be gathered from the intervention group.

For community volunteers involved in the *Connect Local* program, as per Tables 2, 3, we will collect health-related quality of life and wellbeing measures at baseline, 3, 6 and 12 months.

Perceptions of the program will be collected from community members in the intervention group, volunteers and service providers involved in referred to the *Connect Local* program through interviews or focus groups at three months from participant baseline. Questions will invite participants to share their thoughts around the following aspects of the program: Relational (trust and trustworthiness, obligations and expectations, identity and identification), Cognitive (shared language, codes and narratives; shared values, attitudes and beliefs; and shared goals and purpose), and Structural (roles, rules, precedents and procedures).

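### Volunteers enrol only after they have begun supporting Connect Local participants, so their baseline is taken during exposure and change from it may understate or misattribute the effect hypothesised in section 3.1

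*Protocol article*

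**What the plan says.** Section 3.1 (Program effectiveness) states the volunteer hypothesis: "Three months after participation in the program, community volunteer participants will have improved wellbeing and quality of life when compared to baseline".

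Section 3.5.3 (Community volunteers) sets who may enter. One inclusion criterion is that the person is "currently a volunteer engaging with community members receiving" the Connect Local program. The recruitment paragraph in the same section has volunteer organisations pass on the study information. The invitation goes to "all volunteers who have been involved in supporting individuals engaging in" the program, and they contact the researchers themselves.

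Section 3.6.2.1 (Individual level) gives the schedule for volunteers: "we will collect health-related quality of life and wellbeing measures at baseline, 3, 6 and 12 months". Table 2 names the instruments, EQ-5D-5L and WEMWBS. Table 3 lists a baseline visit but does not tie it to the date a volunteer starts.

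A comparator is described in section 3.5.2, for older community members only: "the inclusion criteria for the comparator group are the same as for the intervention group, except that they do not live in the target LGA". None is described for volunteers.

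**The concern.** A within-person comparison speaks to the effect of taking part only if the first measurement precedes taking part. Here the entry rule and the invitation both place enrolment after the first supported contact. The baseline then already contains any early gain or loss, and the three-month visit falls three months after enrolment, not three months after starting.

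The change from baseline is the only quantitative evidence planned for the volunteer hypothesis; the interviews cover perceptions of the program. If wellbeing rises soon after people start and then levels off, the measured change will be close to zero even though volunteering helped. If wellbeing slips back later, the measured change could be negative. In either case a reader could mistake the result for the effect of participating. Volunteer outcomes are a declared aim: they appear in the Abstract, and the Discussion says the evaluation will determine impacts on volunteers.

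**Working it through.** The article gives no sample size, expected effect, standard deviation or power for volunteers, so there is no figure to reproduce. The check is a comparison of the sections, followed by the algebra of what each contrast measures.

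**Sections side by side**

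| Element | Source | Position relative to first supported contact |
|---|---|---|
| Hypothesised contrast: baseline against three months after participation | 3.1 | Needs a baseline before, or at, the start |
| Eligibility: already supporting a recipient | 3.5.3 | After the start |
| Invitation: those who have given support | 3.5.3 | After the start |
| Measures at baseline, 3, 6 and 12 months | 3.6.2.1, Tables 2 and 3 | Not tied to the start |
| Limit on time since starting, or retrospective pre-measure | Not described | – |
| Volunteer comparator | Not described | – |

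Anyone who meets the entry rule as written has had some exposure at baseline. How much is not stated.

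**What each contrast measures**

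Let W(s) be mean wellbeing s months after the first supported contact, with W(0) just before it, and let t be the delay from that contact to enrolment.

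- Effect of participating at three months: W(3) − W(0).
- Measured change from enrolment to the three-month visit: W(t+3) − W(t).
- Measured minus intended: [W(t+3) − W(3)] − [W(t) − W(0)].

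The second bracket is the change already made before enrolment. The first is any further change between month 3 and month t+3. The two contrasts agree when t = 0, or when the brackets happen to cancel.

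**Range, under a stated assumption**

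Suppose a fraction f of the total gain has accrued by enrolment and all the rest accrues by the three-month visit, with no later decline. The measured change is then (1 − f) times the total gain:

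- f = 0: 1 − 0 = 100%
- f = 0.25: 1 − 0.25 = 75%
- f = 0.5: 1 − 0.5 = 50%
- f = 0.75: 1 − 0.75 = 25%
- f = 1: 1 − 1 = 0%

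The documents give neither f nor t. The range shows only that the result could run from no loss to complete loss of the effect. If wellbeing declines after an early gain, the measured change can fall below zero.

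**The case against.** The strongest reply is that section 3.1 speaks of change from baseline and never says that baseline precedes volunteering. A baseline and a three-month measure are both planned, so the stated comparison can be carried out. This stands. A reader might infer that the hypothesis cannot be tested at all, and the documents do not support that. What is lost is the reading of the change as the effect of participating.

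Next, the delay may be short. Section 1.1 describes the program as newly developed, so nobody has long Connect Local service at launch. This also stands in part, but it does not limit the delay for volunteers invited later, and no limit is stated. An article may leave visit timing to a fuller protocol. The eligibility wording is printed here, however, and by itself it places entry after the start.

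A reader might also infer that volunteers who stopped are excluded, leaving those who found it rewarding. Section 3.5.3 is ambiguous on this: the criterion requires current volunteering, while the invitation covers people who have been involved. Why people stop is not addressed. The selection argument is therefore not relied on.

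The direction of the bias is open too. With an early gain that levels off, it runs against the hypothesis and would not create a false benefit. Nor does the article say that the change will be reported as a causal effect; the volunteer research question in 3.1 concerns perceptions and experience.

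Finally, a baseline before first contact would still be an uncontrolled before-after comparison. That is true. Moving the baseline removes one identifiable bias and does not supply a comparator.

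**Conclusion.** The concern holds in a limited form. As written, section 3.5.3 gives every eligible volunteer a baseline taken after exposure has begun, at an unstated and varying time since starting. The planned change from baseline to three months is computable, but it is change during ongoing volunteering and may understate or misattribute the effect of participation hypothesised in section 3.1.

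The size of the bias cannot be fixed from the documents. It depends on the delay between first contact and enrolment and on the time course of any effect, and neither is given. If volunteers enrolled within days of starting, the loss could be small, but nothing in the article ensures this.

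The consequence is confined to the volunteer component, which is secondary. The primary UCLA-3 comparison in older participants is untouched. Sections 3.1 and 3.5.3 should be reconciled before the volunteer change scores are interpreted.

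**What to change.** Amend section 3.5.3 so that volunteers who have agreed to support a Connect Local participant, but have not yet begun, can enrol. The same organisations would give the invitation at induction or first assignment. Baseline WEMWBS and EQ-5D-5L would be completed before the first supported contact, and the three months counted from that contact.

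Record the volunteering start date for everyone. Volunteers already active at enrolment can still take part, including in the interviews. Report their scores separately and descriptively, as change from enrolment by time since starting, and do not use them to test the hypothesis in 3.1.

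If enrolment before first contact is not workable, restate the hypothesis as change from enrolment among active volunteers and still record start dates.

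The main cost is fewer volunteers in the before-after analysis, which remains uncontrolled. There is also some operational burden: recruitment relies on volunteers contacting the researchers through outside organisations, which would need to pass on the invitation early enough for the baseline to be completed in time.

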#### Health and social service providers

3.5.4

Inclusion criteria are individuals who work at health and social services that support eligible older participants or volunteers in the target LGA, including the *Connect Local* program and the Community Connectors. Researchers will obtain information on health and service providers engaged in the program from the Community Connector and contact them directly to ask them to participate in the evaluation.

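### Section 3.5.3 contradicts itself on former volunteers and recruits volunteers only by self-referral, so the volunteer findings on experience of the program are likely to look too favourable

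*Protocol article*

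**What the plan says.** Section 3.5.3 of the protocol article sets out who counts as an eligible volunteer and how volunteers enter the evaluation.

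- **Eligibility.** The person must be "currently a volunteer engaging with community members receiving" the Connect Local program.
- **Invitation.** "Organisations engaging volunteers will share the information on the evaluation", and the people to be invited are "all volunteers who have been involved in supporting individuals engaging in" the program.
- **Route of entry.** Those volunteers "will be invited to reach out to researchers and participate in the evaluation".

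Section 3.1 states two hypotheses that involve volunteers. One is that "all stakeholders: intervention, volunteer and service provider participants will also have a positive perception of and experience with the program". The other is that, three months after taking part, "community volunteer participants will have improved wellbeing and quality of life when compared to baseline".

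Volunteers' perceptions come from interviews or focus groups at three months (Table 2 and section 3.6.2.1). Their wellbeing (WEMWBS) and quality of life (EQ-5D-5L) are measured at baseline, 3, 6 and 12 months. Stakeholder views also feed the acceptability findings (section 3.6.4.2) and the fidelity and sustainability findings (section 3.6.4.3).

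**The concern.** A hypothesis that volunteers view the program positively is only as credible as the sample of volunteers who are asked. Two features of section 3.5.3 bear on that sample.

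First, if the eligibility rule is applied as written, anyone who tried the role and gave it up before enrolment is shut out. Those people are among the likeliest to have had a neutral or poor experience. They are also the ones who can say why volunteers stop, which matters for sustainability in a program that relies on volunteer support to supplement the paid Community Connector (section 1.2).

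Second, a volunteer enters only by taking the initiative. Willingness to do so is plausibly related to how the experience went.

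Both features push in the direction of the hypothesis. No volunteer comparator is described, so no contrast would offset the selection.

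**Working it through.** The plan states no figure on this point: no volunteer sample size, retention rate or response rate. The check is therefore a comparison of the text, followed by one illustration on assumed inputs.

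**1. Eligibility against invitation (both in section 3.5.3).** The criterion is in the present tense and covers people volunteering now. The invitation is in the perfect tense and covers anyone who has ever supported a participant. A former volunteer passes the second and fails the first. The section does not say which prevails.

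**2. Route of entry, group by group.**

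| Group | Section | Who makes the contact |
|---|---|---|
| Older people, intervention | 3.5.1 | Researchers, after the person agrees to share details |
| Older people, comparator | 3.5.2 | Researchers; individuals "will be asked if their details can be shared with the researchers to contact them about the study" |
| Health and social service providers | 3.5.4 | Researchers, who "contact them directly to ask them to participate in the evaluation" |
| Volunteers | 3.5.3 | The volunteer |

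Volunteers are the only group who must act first.

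**3. Which hypothesis is exposed.**

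- *Perception and experience.* This is assessed once, without a volunteer comparator, among those who come forward. Having left, and not coming forward, are both plausibly related to the quality of the experience. The exposure is direct.
- *Wellbeing and quality of life.* This is change from baseline within enrolled volunteers. Selecting satisfied people at entry affects whose change is measured, but does not by itself inflate that change. No bias follows from the text.

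**4. Illustration, all inputs assumed.** Let *p* be the true share of volunteers with a positive experience, and *r* the participation rate of satisfied volunteers divided by that of dissatisfied ones. The share seen among participants is

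observed = *p·r* / (*p·r* + 1 − *p*).

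| Assumed *p* | *r* = 1 | *r* = 1.5 | *r* = 2 | *r* = 3 |
|---|---|---|---|---|
| 50% | 50% | 60% | 67% | 75% |
| 60% | 60% | 69% | 75% | 82% |

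For example, with *p* = 0.6 and *r* = 2: 1.2 / (1.2 + 0.4) = 0.75. The table shows direction and mechanism only. The documents give neither *p* nor *r*, and they define no such proportion, because perceptions are analysed thematically (section 3.7.1.2).

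**The case against.** Several points on the other side are sound.

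- **Current volunteers who are unhappy are not excluded.** They are eligible and invited. A reader might infer that dissatisfied volunteers drop out of the sample by rule; the text does not say so. Their under-representation is a likely effect of self-referral.
- **Nobody is removed for stopping after enrolment.** Being a current volunteer is an entry criterion. Nothing in the article ties follow-up to continued volunteering, so a reader who infers that later leavers are lost goes beyond the text.
- **Bias in the wellbeing hypothesis is not shown,** for the reason given in step 3. Enrolling people who had already left would also harm that analysis, because their baseline would fall after their exposure had ended.
- **Other groups also opt in.** Older people in both arms must agree to share their details. The difference from volunteers is one of degree, although who makes the contact remains a real difference.
- **The primary outcome does not depend on volunteers.** It is UCLA-3 loneliness in older people against the comparator group.

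The objection that an article condenses the full protocol does not dispose of the point. The article states both the eligibility rule and the route of entry, and the first disagrees with the invitation beside it.

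**Conclusion.** The point stands in a limited form. Section 3.5.3 is inconsistent on former volunteers, and its self-referral route differs from that of every other group. Followed as written, it excludes volunteers who stopped before enrolment and probably under-samples less satisfied ones. The volunteer part of the positive-experience hypothesis, and the acceptability and sustainability findings that draw on volunteers' views, are then likely to look too favourable.

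This rests on two assumptions: that leaving the role and not coming forward are both related to a poorer experience, and that the narrower eligibility wording is the one applied. If the broader invitation governs, the exclusion of former volunteers disappears and only the effect of self-referral remains. The size cannot be derived from the documents. The point does not extend to within-person change in wellbeing or quality of life, nor to the trial's primary comparison.

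**What to change.** In section 3.5.3, separate the two uses of the volunteer sample.

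1. **Perception interviews or focus groups.** Make eligible anyone who has volunteered with at least one Connect Local community member, whether or not they still do. This settles the contradiction in favour of the broader group.
2. **Contact.** Have the volunteer organisations ask each such person for permission to pass their details to the researchers, who then make the approach. This is the route already used in sections 3.5.1 and 3.5.2.
3. **Wellbeing and quality of life.** Keep the WEMWBS and EQ-5D-5L baseline-to-follow-up cohort to people enrolled while volunteering, so that the baseline is not taken after the role has ended.

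The cost is a wording change, a little researcher time and probably an ethics notification. The responses obtained may be less favourable.
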